18	Recruitment status: enrolling by invitation
19	Primary outcome(s): delirium prevalence, measured by daily delirium screening (I-Confusion Assessment Method-based scoring system for delirium severity (I-CAM-S)) over 7 days post surgery, as well as after 2 and 6 months; Nursing Delirium Screening Scale (NuDESC) on days 2 and 6 post surgery
20	Key secondary outcome(s): delirium duration as described in the primary outcome assessment. Prevalence of POCD 2 and 6 months after surgery as measured by a neuropsychological test battery (Montreal Cognitive Assessment (MoCA), digit span backwards and Trail Making Test A and B (TMT A and B)) as well as cognitive performance measured with the continuous nonstandardized test values of these scales. A cognitive deficit is defined as the presence of a test value ≤ 0.5 standard deviations, normalized for age, gender, and education, in one of these test procedures

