The *secondary outcomes* will be: delirium duration as described in the primary outcome assessment; prevalence of POCD 2 and 6 months after surgery; and persistence of POCD after 12 months. The prevalence of POCD will be measured by the following neuropsychological test battery: the Montreal Cognitive Assessment (MoCA) [35], the digit span backwards [36], the Trail Making Test A and B (TMT A and B) [37], and cognitive performance measured with the continuous nonstandardized test values of these scales. A cognitive deficit is defined as the presence of a test value of ≤ 0.5 standard deviations, normalized for age, gender, and education, in one of these test procedures.

The MoCA is a brief cognitive screening test for assessing cognitive impairment among older people. The test assesses multiple cognitive domains including visuospatial ability, executive functions, memory, attention, language, abstraction, and orientation. The MoCA has high sensitivity (0.90) and specificity (0.87) to detect individuals with mild cognitive impairment and distinguish them from cognitively intact older people [35] and is available in three parallel versions.

The digit span backwards is commonly used to assess working memory capacity. Participants are required to recall a sequence of spoken digits in reverse order. For people older than 70 years, the digit span backwards had a test–retest reliability > 0.60 and an internal consistency of 0.882 [38].

The TMT is a widely used instrument in neuropsychological assessment that measures the speed of scanning and visuomotor tracking, divided attention, and cognitive flexibility [36]. The test consists of two parts, A and B. TMT A requires an individual to draw lines sequentially connecting consecutive numbers from 1 to 25. TMT B involves drawing a similar line, connecting an ascending sequence of numbers and letters in an alternating manner. In a sample of healthy older adults, Part A had a test–retest reliability of 0.78 and Part B of 0.73, and Part A an inter-rater reliability of 0.99 and Part B of 0.93 [39]. In a sample of elderly volunteers, Part B had a sensitivity of 0.63 for cognitive dysfunction, 0.72 for dementia, and 0.77 for AD, and a specificity of 0.89 [40].

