#### Sample size

The power analysis for the primary outcome of delirium prevalence assumes a reduction in the outcome from 25% to 15% [20] as a result of the intervention. A conventional analysis to detect differences in proportions (delirium rate) between the intervention and control groups, using Fisher’s exact test, results in a total of 514 patients with a 1:1 randomization, given a power of 1 – β = 0.80 and an α error of 5%. Using the adjustment form proposed by Woertman et al. [67] with five crosspoints in a stepped-wedge design, with a maximum of 50 patients per cluster per period and an intracluster correlation of 0.01, leads to a correction factor for the stepped-wedge design of KF = 2.63, and therefore a number of 514 × 2.63 = 1351 patients. Assuming a dropout rate of 15%, this leads to a total requirement for about 750 patients per arm. The minimum number of clusters is given by the ratio of the total number of patients to the product between the number of crossing points and the patients per cluster per period, and is 15.

For the secondary outcomes, a reduction of the persistent cognitive deficit from 20% to 10% results in 428 patients using the conventional analysis with Fisher’s exact test and a 1:1 randomization, a power of 1 – β = 0.80, and an α error of 5%, which after the design correction leads to a requirement of 1079 patients.

Thus, the planned sample size is of at most 1500 patients (see Fig. 1 with the numbers per period). Furthermore, relatives of the patients will be asked about the burden of caring and the cognitive status of the patients.

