#### Ethics

This is an intervention study in which existing guidelines and recommendations will be implemented, including the S3 guideline of the German Society for Anesthesiology and Intensive Care Medicine (Deutsche Gesellschaft für Anästhesie und Intensivmedizin (DGAI)), the S3 guideline of the Working Group in Geriatric Traumatology (Arbeitsgemeinschaft Alterstraumatologie (AG Alterstraumatologie)) of the German Association of Trauma Surgery (Deutsche Gesellschaft für Unfallchirurgie (DGU)), the guidelines of the National Institute for Clinical Excellence (NICE), the guidelines of the American Geriatrics Society (AGS), and the guidelines of the Difficult Airway Society (DAS). Ethics approval according to the occupational regulations (Berufsordnung (BO)) has been obtained for all centers. All relevant changes will be communicated to the scientific advisory board, the Regional Ethics and Data Monitoring Board (REDMB), the relevant institutional review boards (IRBs), and the clinical trial registry. Given that there are no extra risks, the usual health insurance or civil liability will cover the risks of the trial, and there will be no additional medical liability insurance for the study. For the additional outpatient assessments, patients and their relatives will be covered by travel insurance.

In the preadmission assessments, it is to be expected that approximately 40% of the examined patients will have slight or severe cognitive impairment [72]. However, this does not necessarily restrict their capacity to consent or their legal capacity. Following Kim and Caine [73], we consider that this only occurs when transitioning to a more severe dementia (MMSE < 19). For those patients, the possible damage would be the self-stigmatization as a dementia-endangered person, but the benefit of the intervention would prevail because of its stipulated reduction of delirium and POCD.

On the other hand, if a previously unrecognized severe cognitive disorder was found, the patient probably could not consent, requiring consent from a substitute decision-maker.

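### The only case rule given for POCD (one test at an unsigned 0.5 SD norm cut-off, with no reference to the preoperative score) does not identify decline and does not fit the planned rates

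*Protocol article*

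**What the plan says.** Under Outcome assessment, the secondary outcomes include "prevalence of POCD 2 and 6 months after surgery; and persistence of POCD after 12 months". The battery is the MoCA, digit span backwards, and TMT A and B. The case rule follows: a deficit is any value at or below 0.5 "standard deviations, normalized for age, gender, and education, in one of these test procedures". Item 20 of Table 1 repeats it: "A cognitive deficit is defined as the presence of a test value ≤ 0.5 standard deviations". Neither place gives a sign, a direction for each test or a role for the preoperative value. The same sections also list the continuous, non-standardised test values as an outcome.

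Four other places bear on the rule:
- Design states the aim as a lower rate of postoperative cognitive decline.
- Background says that POCD has been studied against the state before surgery.
- Ethics expects that "approximately 40% of the examined patients will have slight or severe cognitive impairment" at the preadmission assessment.
- Sample size plans on "a reduction of the persistent cognitive deficit from 20% to 10" per cent.

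**The concern.** A cut-off half a standard deviation from the norm mean lies well inside the normal range, and needing only one failed test out of several makes the rule more lenient still. With no preoperative comparison, a patient who was impaired before surgery and has not changed is counted the same as one who has declined. Cases that the intervention could not have prevented then fill both arms and shrink the observable difference. POCD is a key secondary outcome, the subject of one of the three stated aims, and the unit of the insurer analysis, whose target parameter is the cost per avoided POCD.

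**Working it through.** **Inputs from the article.** Cut-off 0.5 SD, one test sufficient, four scores (or three procedures if TMT A and B count as one). Planning rates 20% and 10%, conventional total 428, power 0.80, alpha 5%. Design factor 2.63, at most 1500 patients, dropout 15%. Retest reliability above 0.60 (digit span), 0.73 (TMT B) and 0.78 (TMT A).

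**Assumptions.** The article gives no correlation between the tests. I take standard-normal norm scores with a common correlation ρ and show a range.

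**1. The plan's own figure.** The two-sided Fisher exact test with 214 per arm, 20% against 10%, has 80.1% power. The stated 428 reproduces, so the arithmetic is sound for those rates. The question is whether the rule can yield them.

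**2. Share of a norm population flagged at one visit.** One test at -0.5 SD: Φ(-0.5) = 0.309. For k independent tests: 1 - (1 - 0.309)^k, which is 0.77 for k = 4 and 0.67 for k = 3. For correlated tests: 1 - ∫ [1 - Φ((c - √ρ·u)/√(1 - ρ))]^k φ(u) du.

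| Cut-off c | Tests k | ρ = 0 | 0.3 | 0.5 | 0.7 |
|---|---|---|---|---|---|
| -0.5 | 4 | 77% | 67% | 60% | 53% |
| -0.5 | 3 | 67% | 59% | 54% | 48% |
| +0.5 | 4 | 99% | 96% | 92% | 88% |
| +0.5 | 3 | 97% | 93% | 89% | 85% |

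With perfectly correlated tests the share at -0.5 SD is still 31%. For any-of-four to flag 20% of a norm population, the cut-off would have to lie between about -1.60 SD (ρ = 0) and -1.34 SD (ρ = 0.7).

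**3. What the missing baseline does.** I simulated norm patients with no true change (400,000 per setting; c = -0.5; four scores; ρ 0.3 to 0.7; retest correlation 0.60 and 0.75).

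| Definition of a case | Share flagged |
|---|---|
| Deficit at one follow-up visit | 53 to 67% |
| Deficit at all three follow-up visits | 30 to 49% |
| Deficit at one follow-up visit, absent before surgery | 12 to 15% |
| Deficit at all three follow-up visits, absent before surgery | 4 to 6% |

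Of the cases in the first row, 71 to 82% already met the rule before surgery.

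**4. Illustration of the dilution.** Suppose true rates of 20% and 10%, with a share f of all other patients flagged in both arms. The observed rate is p + (1 - p)f. For f = 0.6 this is 0.2 + 0.8 × 0.6 = 0.68 against 0.1 + 0.9 × 0.6 = 0.64. After dropout, 1500 × 0.85 = 1275 patients remain; dividing by 2.63 leaves 485, or about 242 per arm. Normal-approximation power for two proportions, two-sided 5%:

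| f | Observed rates | Power |
|---|---|---|
| 0 | 20% vs 10% | 87% |
| 0.50 | 60% vs 55% | 20% |
| 0.60 | 68% vs 64% | 15% |
| 0.65 | 72% vs 68.5% | 13% |

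**The case against.** The strongest reply is that the article defines a cognitive deficit and never says in so many words that POCD is a deficit at follow-up alone. Its aims and background speak of decline and of the preoperative state, and a fuller document may supply the link. The 20% to 10% refers to a persistent deficit, for which the article gives no rule. If a deficit must be new since surgery, only 12 to 15% of unchanged norm patients are flagged, which leaves room for a 20% control rate. The continuous scores are in any case an outcome that needs no cut-off.

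Much of this stands, and it limits the point in four ways:
- A reader might infer that the planned rates are impossible. The documents do not support that, because the outcome depends on a baseline condition that is not stated.
- A reader might infer that most healthy older people would be labelled as cases. That needs ρ below about 0.76 with four scores, and it already fails at 0.7 with three procedures.
- The power figures illustrate the follow-up-only reading at an assumed f. They are not a forecast.
- False positives that are equally common in both arms do not by themselves bias the comparison.

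What does not stand is that this is mere omission. The rule is stated twice and is the only one given. Persistence alone does not rescue it: with no baseline condition, a deficit at all three visits still flags 30 to 49% of unchanged norm patients.

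**Conclusion.** The point holds in this form: the case rule as written is unsigned, lenient and cross-sectional, and it disagrees with the article's own aim, background and planning rates. The firm figure is 31% of a norm population flagged by a single test at -0.5 SD, already above the planned 20% control rate at one visit. The wider ranges (53 to 77% for four scores, 48 to 67% for three procedures) rest on assumed correlations of 0.7 to 0. The literal +0.5 SD reading (85 to 99%) most likely reflects a dropped minus sign, but the text has to say so. With about 40% expected to be impaired before surgery, the norm population is a favourable case. The harm is loss of power and a blurred meaning for POCD and for the cost per avoided case. The primary delirium outcome is not affected.

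**What to change.** - Define POCD by reference to the patient's own preoperative score: for example, a deficit present after surgery and absent before it, or a standardised decline from baseline. A practice-corrected change of z ≤ -1.96 is one option but is not required, and it would need a retest reference that the article does not describe.
- State the sign and size of the cut-off, the direction for each test (longer TMT times are worse), whether TMT A and B count once or twice, and how many tests must be failed.
- State what persistence at 12 months requires.
- Analyse the already planned continuous scores with adjustment for the preoperative score.
- Keep the norm-based deficit as a descriptive measure.
- Bring Table 1, Outcome assessment, Design and Sample size into line, with planning rates that suit the chosen rule.

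If the full battery is given before surgery, this costs only wording and analysis. That needs confirming: the baseline list does not name the MoCA, digit span or TMT, and Fig. 3, which may show them, is not available here. There will be fewer cases, and patients without preoperative scores drop out of the binary endpoint.

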**Fig. 3 Fig3:**
[figure not shown]
Standard Protocol Items: Recommendations for Interventional Trials figure of enrollment, intervention, and assessments. CSHA Clinical Frailty Scale of the Canadian Study of Health and Aging, EQ-5D-5L EuroQol five dimensions questionnaire, G-ZBI German Zarit Burden interview, I-CAM-S I-Confusion Assessment Method-based scoring system for delirium severity, IQCODE Informant Questionnaire on Cognitive Decline in the Elderly, MNA-SF Mini Nutritional Assessment Short Form, MoCA Montreal-Cognitive Assessment, NOSGER II Nurses’ Observation Scale for Geriatric Patients, NRS Pain Numerical Rating Scale of Pain, NuDESC Nursing Delirium Screening Scale, PHQ-4 Patient Health Questionnaire, PSQI (Basic) Pittsburgh Sleep Quality Index (Basic), RASS Richmond Agitation–Sedation Scale, SF-12 12-Item Short Form Survey, SMI subjective memory impairment, TMT Trail Making Test, V1/V2/V3 parallel versions of the MoCA, STOP BANG Sleep Apnea Questionnaire (snoring, tiredness, observed apnea, blood presure, body mass index, age, neck circunference, gender)

For *planned validity assessment of postoperative delirium*, the validity of the I-CAM-S and NuDESC vs the Richmond Agitation-Sedation Scale (RASS) [66] and vs chart review will be evaluated. The RASS is a simple observational scale that quantifies the level of consciousness, assessing both sedation and agitation.

For *analysis of delirium severity*, the duration and extent of restraints and one-to-one supervision requirements will be used, in addition to the CAM-S score.

For *process analysis*, acceptance and feasibility will be evaluated by qualitative assessment using focus groups formed by members of the geriatric centers.

For *planned health-economic analyses*, the initial hospital costs and the costs per delirium of two centers (Tübingen and Stuttgart) will be assessed. Moreover, for the patients whose health insurance is AOK Baden-Württemberg (Germany), health and care insurance expenditures and utilization will be assessed, in particular regarding hospital care, outpatient care, medication, rehabilitation, and nursing care. For a precise evaluation of the costs, the expense for training and staff carrying out the intervention will be included in the analyses.

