#### Intervention

The intervention implements a cross-sectoral all-encompassing multimodal delirium prevention and management approach, and will be carried out in each study center after the center is randomized to take part in the intervention phase of the trial:All personnel training: within 4–6 weeks before the start of the intervention phase, nurses and therapeutic, medical, and support staff involved in the care of study patients will be trained with respect to dementia and delirium care, delirium diagnosis, and depression using a standardized training plan. Staff will be trained to three different levels of expertise: more than 70% of the staff are to receive basic training (90-min training time); more than 20% of nurses are to receive advanced training (“delirium scout” training—450-min training time); and more than 10% are to receive expert-level training (“delirium champion” training—900-min training time). Additionally, at least 70% of the physicians will receive 90 min extra of specific training about delirium risk, diagnosis, treatment, and prevention. The courses will be adjusted to the specific surgical and anesthesiological departments and special care units in order to ensure comparable levels of knowledge between different study sites.Environmental orientation support: the hospital environment will be adapted to the special needs of the patients. The decline of sensory function in older adults often leads to additional psychosocial stress, and is exacerbated by cognitive impairment. To address these issues, appropriate posters and signage will be placed on the wards, and in patients’ rooms and restrooms. Tools for temporal and situational orientation will be made available; for example, whiteboards with personal information, date, season, and year, as well as analog clocks that can be seen from the bed. Moreover, appropriate tools to prevent falls will be provided, such as anti-sliding socks. Special boxes for glasses, hearing aids, and dentures, as well as sleeping masks and ear plugs will be within reach of the patients at all times.Preadmission phase: the trained staff will implement some nonpharmacological preventive interventions in this phase, including informative talks and written recommendations for patients, and instructive contacts with the referring doctors regarding the age-appropriateness of prescribed medications and interventions.“Best practice” multimodal intervention: participants at the respective centers will receive perioperative and postoperative multimodal delirium prevention and care management between 8 a.m. and 8 p.m. on 7 days of the week, modified according to best practice models such as the Hospital Elder Life Program (HELP) [26], “The old patient in the surgery room” [22], or the Care of Confused Hospitalised Older Persons (CHOPs) [27]. Psychogeriatric nurses and one physician who have received 900 additional minutes of “delirium champion” training will form a multiprofessional consultation–liaison-like intervention team that will contact the patients and address their special needs daily. They will facilitate the implementation of the treatments advised in international delirium prevention guidelines [17, 23]: adaptation of surgery and anesthesia, medication and pain treatment appropriate for the patients’ age, pain monitoring, avoidance of movement restrictions such as catheters or infusions, and avoidance of benzodiazepines and anticholinergic drugs. These specialists will prescribe meaningful individualized daily activities for preventing delirium, defined in six modules: reorientation, cognitive activation, mobilization, meal companionship, clinical diagnostics and operation room attendance, and nonpharmacological sleep promotion and anxiety reduction. A team of nurses’ aides or volunteers (mostly gap-year social work volunteers) will carry out these activities, as well as chaperone patients during the diagnostic procedures, and in the operating and recovery rooms. They will receive 40 h of theoretical and practical training on the modules, and will be available daily in two shifts of 12 h per day.Patients and their family members will be advised individually about delirium risk and prevention, and will receive information materials (leaflets, posters, etc.) about delirium and the care service. Moreover, family members will provide individual information about the patient, facilitating individualized care and communication, and will be advised to support some individualized delirium prevention activities.

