#### Outcome assessment

The assessment of all the outcomes will always be performed by trained assessors, who will be blinded for the intervention. Specifically, delirium raters will be told that the data will be used for validating a delirium risk score. Staff will be instructed not to reveal the nature of the intervention to these assessors.

The *primary outcome* will be delirium prevalence. It will be measured by daily delirium screening (I-Confusion Assessment Method-based scoring system for delirium severity (I-CAM)/CAM-S)) [28, 29] over 7 days after surgery and after 2 and 6 months, the Nursing Delirium Screening Scale (NuDESC) [30] (days 2 and 6 after surgery), a chart review at discharge applying the DSM-V delirium criteria as a reference standard [31], and the clinical evaluation.

The CAM [32], with its four-step diagnostic algorithm, is a widely used screening test for assessing delirium. Originally developed from the DSM-III-R, it is now predominantly used for delirium screening and research according to the DSM-IV and DSM-V criteria. It has been operationalized and translated into German [33], and then revealed a high sensitivity of 0.77 in a cohort of geriatric patients with a high prevalence dementia, and a specificity of 0.96–1.00 with excellent inter-rater reliability (Cohen’s κ = 0.95 (CI 0.74–1.0) for the algorithm, single item’s κ values varied between 0.5 and 1).

The I-CAM (I for ICD-10) [28] extends the German version of the original CAM adding abnormal psychomotor activity, to allow taking also the ICD-10 delirium diagnosis as a reference standard and assessing the motor delirium subtypes as well. The CAM-S [29] is a CAM-based scoring system for assessing delirium severity and was operationalized for use with the German version of the I-CAM. As the CAM might be confounded by the fluctuating nature of delirium, we use a chart-based review [31] filled out by trained medical staff at discharge to evaluate for fluctuations in sleep–wake rhythm or psychomotor activity indicating delirium.

The NuDESC is a five-item scale based on nurses’ observations assessing disorientation, inappropriate behavior and communication, hallucinations, and psychomotor retardation over a 24-h period. For the German version of the NuDESC, in a sample of patients after elective surgery, a sensitivity of 0.98, a specificity of 0.92, and an inter-rater reliability of 0.83 were observed [34].

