
For *planned analysis*, the following variables are currently anticipated: anxiety and depression will be evaluated with the PHQ-4 questionnaire, the health-related quality of life with the EQ-5D-5 L questionnaire and the SF-12 survey, the nutrition status with the MNA-SF, the functional status with the Barthel Index, and the frailty with the CSHA Clinical Frailty Scale and hand grip. The duration and extent of use of physical restraints and patient care attendants will also be assessed. Moreover, the relevant aspects of behavior in daily life will be assessed by the Nurses’ Observation Scale for Geriatric Patients (NOSGER II) [64, 65], the presence of cognitive decline will be assessed by IQCODE evidenced by relatives, and the subjective burden of family caregivers by G-ZBI. The timelines are summarized in Fig. 3.

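### Two of the three delirium-severity measures, restraint use and one-to-one supervision, are care processes that the intervention can change, so they cannot show a difference in severity between phases

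*Protocol article*

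**What the plan says.** The paragraph on delirium severity, after Fig. 3 in the Outcome assessment section, names three measures: "the duration and extent of restraints and one-to-one supervision requirements will be used, in addition to the CAM-S score". It gives no rule for combining them.

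Earlier in the same section, CAM-S is introduced as a severity instrument in its own right; it "is a CAM-based scoring system for assessing delirium severity and was operationalized for use with the German version of the I-CAM". The planned-analysis paragraph lists the two care markers as variables too: "The duration and extent of use of physical restraints and patient care attendants will also be assessed".

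The Intervention section describes what changes when a center crosses over. Among the treatments that the liaison team facilitates is "avoidance of movement restrictions such as catheters or infusions". Nurses' aides or volunteers carry out the prescribed activities and also "chaperone patients during the diagnostic procedures, and in the operating and recovery rooms"; they "will be available daily in two shifts of 12 h per day". The comparator is the usual care that a center gives before its randomized start. Outcome assessors are to be blinded.

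**The concern.** A severity measure must mean the same thing in both phases. Restraint use and one-to-one supervision are responses of the ward to a patient, and they depend on staffing, training and policy as well as on symptoms. The intervention acts on those determinants. If fewer restraints in the intervention phase were reported as milder delirium, the trial could be describing its own change in care practice. If companions replaced sitters, or were recorded as sitters, the supervision marker could move down or up with no change in the patients. What is at stake is the reading of a supplementary severity analysis. The headline result on delirium prevalence is not involved.

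**Working it through.** **1. The measures set against the intervention**

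| Measure | What it records | Who determines it | Does the intervention act on it directly? |
|---|---|---|---|
| CAM-S | Symptoms | Blinded trained assessor | No; it changes only if symptoms change |
| Restraints, duration and extent | Care given | Treating staff | Plausibly: avoiding movement restrictions is part of the programme. The examples are catheters and infusions; physical restraints are not named |
| One-to-one supervision requirements | Care judged necessary | Treating staff | Plausibly: the programme adds companions, absent under treatment as usual. They may replace a sitter or be recorded as one |

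Blinding does not cure this. A blinded assessor who records that a patient was or was not restrained records the decision of staff who were trained in the programme and know that it is running.

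**2. Is any figure in the plan affected?** No. The plan gives no restraint rate, supervision rate or power for severity, so there is no figure to reproduce.

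**3. Illustration of size, with assumed inputs**

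From the Sample size section: about 750 patients per arm, delirium 25% against 15%, design factor 2.63. Assumed, because the documents are silent: restraint use of 10%, 20% or 30% among delirious control-phase patients, and a relative fall of 25%, 50% or 75% caused by care policy alone, with identical symptoms.

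Delirious patients: 750 × 0.25 = 187.5, taken as 188; 750 × 0.15 = 112.5, taken as 112.

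Probability of a significant two-sided 5% difference = Φ[(d − 1.96 × SE0) / SE1], where d = p0 − p1, SE0 uses the pooled proportion and SE1 the separate proportions.

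Example, 20% falling to 10%, no clustering:
- pooled proportion = (188 × 0.20 + 112 × 0.10) / 300 = 0.1627
- SE0 = √[0.1627 × 0.8373 × (1/188 + 1/112)] = 0.0441
- SE1 = √[0.20 × 0.80/188 + 0.10 × 0.90/112] = 0.0407
- Φ[(0.10 − 1.96 × 0.0441) / 0.0407] = 0.63

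With both group sizes divided by 2.63, the same calculation gives 0.27.

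| Control-phase restraint use | Relative fall | No clustering | Sizes divided by 2.63 |
|---|---|---|---|
| 10% | 25% | 0.10 | 0.06 |
| 10% | 50% | 0.32 | 0.14 |
| 10% | 75% | 0.71 | 0.29 |
| 20% | 25% | 0.18 | 0.09 |
| 20% | 50% | 0.63 | 0.27 |
| 20% | 75% | 0.97 | 0.61 |
| 30% | 25% | 0.29 | 0.13 |
| 30% | 50% | 0.85 | 0.43 |
| 30% | 75% | 1.00 | 0.85 |

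With no effect on symptoms, the rate should be 0.05. Carrying 2.63 over to the delirious subgroup is rough, since the protocol derived it for all patients. No such calculation is offered for supervision, because its direction is unknown.

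**The case against.** Much of the case on the other side stands.

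- **No composite is defined.** A reader might infer that restraints and supervision feed into one severity score, so that the comparison is circular and equally delirious patients receive different scores. The text does not say so. The markers are used in addition to CAM-S, which keeps its own value. The problem is confined to the two added markers.
- **An effect on restraints is inferred.** A reader might take it as stated that the programme reduces physical restraint. The Intervention section names catheters and infusions. The list is open-ended, and physical restraint is a movement restriction, so an effect is plausible, but it is not documented.
- **Requirements are not presence.** The severity paragraph speaks of supervision requirements, and nothing says that companion hours will be recorded as such. Nothing excludes it either, and a companion already with the patient may change whether staff see a need for a sitter.
- **Severity is unranked.** It is neither the primary outcome nor a listed secondary outcome, and the paragraph does not state a comparison between phases. This lowers the priority. It does not make the markers valid severity measures if the comparison is made.
- **The protocol partly separates these data already.** It lists restraints and attendants as variables of their own and documents the intervention time daily. That makes the fix cheap.
- **Extra severity information has a rationale.** The protocol notes that the fluctuation of delirium may confound the CAM. Its stated remedy is chart review, and markers that shift with care policy are no substitute between phases.

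Leaving detail to a fuller document is no answer here, because the article itself makes the choice of measures.

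**Conclusion.** The point holds in a limited form. A between-phase difference in restraint use or one-to-one supervision cannot be read as a difference in delirium severity, because the intervention can plausibly change both through care alone and treating staff who know the phase decide on both. For supervision the direction is not predictable.

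No document figure quantifies this. Under the assumptions above, a spurious restraint difference would reach significance with probability 0.06 to 0.85 after the design factor, and 0.10 to 1.00 without it. The result depends on the assumed restraint rate and on how far care policy moves it, and neither is known.

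The CAM-S comparison, the primary outcome and the listed secondary outcomes are untouched. Priority is low to moderate.

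**What to change.** Reword the severity paragraph so that:

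1. Any comparison of delirium severity between phases rests on the assessor-rated CAM-S alone.
2. The CAM-S summary is one that length of stay does not drive, such as the peak score or the mean over assessed days, with the assessment window stated. A raw sum over days 1 to 7 is unsuitable: the Timelines section allows the discharge assessment 1 to 8 days after surgery, so the sum would grow with days in hospital, which the intervention may change. The peak and mean are much less exposed to this, though not wholly immune, hence the stated window.
3. Restraint use and one-to-one supervision are reported as separate care-process or resource-use outcomes.
4. Time supplied by programme companions is not counted as one-to-one supervision.

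The cost is the loss of two supplementary indicators from the severity analysis. The variables are already planned for collection. The main practical demand is a recording rule that keeps companion time apart from supervision ordered by the ward.
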